#### Sample size estimation

Power Analysis and Sample Size Software version 15.0 (PASS, NCSS Statistical Software, Kaysville, UT, USA) was used to determine the study’s sample size. An alpha of 0.05 and a power of 0.9 are used in the study. Based on preliminary trial results, the Clancy Autism Behavioral Scale (CABS) score indicates a curative effect, so the mean and standard deviation of the paired differences are 5 and 8, respectively (15). The PASS software calculation resulted in a minimum requirement of 34 participants per group, accounting for an estimated 20% dropout rate. Considering a 15% rate of invalid MRI data based on previous experience, a minimum of 40 subjects will be recruited per group. Therefore, 40 patients will be enrolled in each group, totaling 80 patients for the study.

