#### Network analysis

The small-world properties, global properties, and local properties of brain networks will be analyzed using graph theory. There are five small-world properties: clustering coefficient (Cp), characteristic path length (Lp), normalized clustering coefficient (Gamma, γ), normalized characteristic path length (Lambda, λ), and small-worldness (Sigma, σ) (50, 51). A network is regarded to have small-world features when γ >> 1, λ ≈1, and σ > 1 (48, 52). Global network properties consist of global efficiency (Eg) and local efficiency (Eloc). Nodal properties, or local properties, include nodal efficiency (NE), betweenness centrality (BC), and nodal degree centrality (DC) (51, 53). A node’s NE can be measured as its capacity to transmit information to other nodes, its BC as its capacity to influence the flow of information between all other nodes, and its DC can be measured as the number of edges it connects with (52, 54).. In a previous publication, these network measures were defined in detail (54).

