### Statistical analysis

Basic analyses will be conducted using SPSS 25.0 software. At baseline, independent samples t-tests will be used to determine if there is no statistical difference between the two intervention groups; paired samples t-tests will then be used to examine the differences between mean scores before and after the taVNS intervention to determine the effectiveness of the treatment. Additionally, for the imaging study, we will use two-sample t-tests to compare brain network parameters between the HC and sham groups, as well as paired-sample t-tests to determine brain network parameters between the sham and active groups. Based on age and gender as covariates, a two-sample t-test will be used to compare the small-world properties and global parameters of the anatomical network between the HC group and the sham group. The level of significance for all statistical tests is set at p< 0.05. A Bonferroni correction will be performed on the t-tests utilized to examine group differences in behavioral and brain measurements, to account for multiple comparisons.

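### Holm's step-down procedure would serve the small test families better than the fixed Bonferroni correction: same 5% family-wise error, never fewer rejections, a gain of 0 to about 9 power points

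*Protocol article*

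**What the plan says.** The Statistical analysis section sets one threshold: "The level of significance for all statistical tests is set at p< 0.05". It then names the multiplicity method: "A Bonferroni correction will be performed on the t-tests utilized to examine group differences in behavioral and brain measurements". No other method is mentioned.

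The measures concerned are spread over three places:
- Table 1 lists five instruments: the high-functioning autism checklist, ABC, CABS, SRS and WISC.
- Network analysis lists five small-world metrics and two global efficiency metrics, seven in all.
- The same section adds three nodal metrics (nodal efficiency, betweenness centrality, degree centrality), each computed at every brain region.

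The sample size rests on one scale, the CABS, at an undivided alpha: "An alpha of 0.05 and a power of 0.9 are used in the study", with "the mean and standard deviation of the paired differences are 5 and 8, respectively".

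**The concern.** Single-step Bonferroni compares every p-value with 0.05/m, where m is the number of tests in the family. Once one hypothesis has been rejected, that threshold is stricter than it needs to be for the rest. Holm relaxes it step by step without raising the family-wise error, so for a given family there is no inferential reason to prefer Bonferroni for the tests themselves.

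What is at stake is power, not validity. The trial has 80 patients, and brain-network remodelling is one of its two stated primary objectives. A child-level effect that shows on several related scales or metrics is the setting in which a step-down method can confirm more of them.

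**Working it through.** **The plan's own figure.** The inputs are mean paired difference 5, SD 8, two-sided alpha 0.05 (sidedness assumed) and power 0.90.
- n = (8 × (1.960 + 1.282)/5)² = 26.9, so 27.
- Dropout: 27/(1 − 0.20) = 33.75, so 34. This matches "a minimum requirement of 34 participants per group, accounting for an estimated 20% dropout rate".
- Invalid MRI: 34/(1 − 0.15) = 40. This matches "40 patients will be enrolled in each group, totaling 80 patients for the study".

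Both stated numbers reproduce at an alpha that is not divided by any number of tests.

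**Why Holm cannot do worse.** Order the p-values from smallest to largest. Compare the j-th with 0.05/(m − j + 1) and stop at the first failure.
- m = 5: thresholds 0.0100, 0.0125, 0.0167, 0.0250, 0.0500. Bonferroni uses 0.0100 throughout.
- m = 7: Holm starts at 0.0071 and ends at 0.0500. Bonferroni uses 0.0071 throughout.
- If a p-value is at or below 0.05/m, so are all smaller ones, and no earlier step fails. Every Bonferroni rejection is therefore a Holm rejection.
- If m₀ nulls are true, the first true null in the order meets a threshold of at most 0.05/m₀. The chance that any of the m₀ falls below that is at most 5%, whatever the dependence.
- The first threshold is 0.05/m in both methods, so whether anything is rejected is always the same.

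**Size in the clinical family.** Assumptions, none of them fixed by the article:
- one family of five instruments;
- two-sample t-tests between arms;
- 40 × 0.80 = 32 completers per arm;
- d = 5/8 = 0.625 on each truly affected scale;
- equal correlation 0.5.

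Results by simulation (100,000 replicates per row):

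| True effects of 5 | Bonferroni, power per true effect | Holm | Gain (points) |
|---|---|---|---|
| 1 | 44.4% | 44.5% | 0 |
| 2 | 44.4% | 46.0% | 2 |
| 3 | 44.6% | 47.9% | 3 |
| 4 | 44.4% | 50.2% | 6 |
| 5 | 44.3% | 53.5% | 9 |

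The exact Bonferroni value, from the noncentral t at alpha 0.01, is 44.3%. At correlation 0 or 0.7 the gains are the same to within half a point. The family-wise error of both methods stayed below 5% in every row that contains a true null.

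**Seven small-world and global metrics.** With 40 × 0.85 = 34 per group, d = 0.625 and correlation 0.5, power per true effect goes from 43% to 43% with one true effect, to 45% with three, 48% with five and 52% with all seven.

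**Nodal families.** Assume 90 regions (not stated), so 90 tests per metric or 270 for all three. Holm's gain is under 0.5 point: for example 16.6% to 17.0% with 20 of 90 true, and 9.8% to 10.0% with 50 of 270 true, both at correlation 0.5.

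Single-step max-T against Bonferroni, at 34 per group and d = 0.625:

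| Tests | Bonferroni | Max-T, ρ = 0 | ρ = 0.3 | ρ = 0.5 | ρ = 0.8 |
|---|---|---|---|---|---|
| 90 | 16.1% | 16.5% | 17.8% | 21.0% | 33.5% |
| 270 | 9.8% | 10.0% | 11.5% | 14.3% | 26.5% |

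At ρ = 0 the exact per-test level for 270 tests is 1 − 0.95^(1/270) = 0.00019, against 0.05/270 = 0.000185, so there is practically nothing to gain.

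**The case against.** The strongest reply is that nothing in the plan is wrong. Bonferroni is valid under any dependence, simple to run and simple to report, and it gives simultaneous confidence intervals directly, which Holm does not. That stands. This is an efficiency improvement to a stated method, not a correction of a mistake.

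Three stronger readings are tempting, and the documents do not support them.

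- *Real effects are lost for nothing, whatever the family.* With a single test the two methods are identical, and with one true effect the gain is nil. The 9-point figure is Holm's best case. It needs an equal effect on all five instruments, including the WISC, an IQ test also used for eligibility. The 0.625 itself comes from a paired difference on the CABS alone.
- *Max-T recovers nodal power at no cost.* The article gives no node count, nodal effect size or correlation. A common correlation of 0.5 or more cannot hold for degree at a fixed sparsity: the total number of edges is then the same for every child, so degrees sum to a constant. With 90 nodes of equal variance the average correlation is −1/89 = −0.011. Max-T also needs a permutation scheme for the age and gender covariates, and sign flips instead of label permutation for paired comparisons.
- *Holm settles the multiplicity question.* It does not say which tests form a family, nor does it bring the correction into the sample size. With the plan's paired inputs and 34 per group, power is 94% at 0.05 and 81% at 0.05/5. Those are separate matters.

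**Conclusion.** The point holds as an efficiency improvement for the small families. Holm's dominance over Bonferroni needs no assumption about the family, the correlation or the form of the t-test. The size of the gain does need assumptions: under those listed, it runs from 0 to about 9 points of power per true effect in a five-scale family, and about the same range (43% to 52% at most) for the seven network metrics. With only some of the scales affected, which is the more plausible case here, expect roughly 2 to 6 points. In the nodal families Holm is of no practical use. Max-T there could give anything from about zero to a substantial gain, and the article does not let one say which.

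**What to change.** In Statistical analysis, replace Bonferroni by the Holm step-down procedure at family-wise 5% for two families: the clinical scales, and the seven small-world and global metrics. List the members of each family in the same sentence, since either method needs m.

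The cost is a change of wording. Sorting at most seven p-values needs no new software, no patients and no change in the error rate. The one loss is simple simultaneous intervals. Intervals at level 1 − 0.05/m can still be reported, with a note that such an interval may include zero for a measure that Holm rejects.

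Bonferroni can stay for the nodal metrics. If the sponsor wants max-T there, the plan must first define the permutation scheme with age and gender as covariates and the sign-flip scheme for paired comparisons, and a script will be needed.

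Make the change before anyone sees outcome data by group. A correction chosen afterwards would not be credible.

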### Clinical trial registry

Beijing Children’s Hospital, Capital Medical University, Ethics Committee approved this randomized controlled trial. The participant and his or her guardian will sign and submit an informed consent form. If participants feel unwell, they can withdraw from the study at any time, and they will be referred to a follow-up doctor for further examination and treatment. The trial has been registered on the Chinese Clinical Trial Registry with the registration number ChiCTR2300074035 (http://www.chictr.org.cn).

## Discussion

This protocol presents a study that evaluates the efficacy of taVNS in children with HFA and explores the associated cerebral network change. To our knowledge, this study may provide new evidence about novel non-pharmacological interventions for ASD. The protocol also aims to examine multiple aspects of the treatment response, going beyond the impact of taVNS on psychosocial functioning and neurophysiological mechanisms.

The treatment approach for ASD typically involves behavioral therapies aimed at reducing problem behaviors and general distress while enhancing social and communication skills. However, these treatments are often unsatisfactory due to high rates of nonresponse, relapse, and occurrence of intolerable side effects (12). Therefore, the exploration of using taVNS to treat ASD, as will be done in our study, will shed light on finding alternative strategies for ASD.

It is currently recognized that there is dysregulation of the sympathetic nervous system in children with ASD, and the vagal tone is low. Decreased vagal activity is associated with the behavioral and linguistic changes present in autism, while higher vagal activity has been linked to improved communication abilities (55). The vagus nerve coordinates the function of the bronchi, lungs, heart, and esophagus (22), regulates the autonomic nervous system, participates in the socio-emotional processes, and also has a role in adaptive behavior (56). Hence, stimulation of the vagus nerve, as in VNS, can change the vagal tone and re-regulate organism function, increase pathologically inadequate vagal response, and modulate the parasympathetic nervous system’s activities in patients with neurodevelopmental disorders (44, 55).

Recently, VNS has been utilized in children with ASD who have co-occurring epilepsy or epileptiform discharges on EEG, demonstrating therapeutic benefits for alleviating clinical symptoms (57). A study involving six children diagnosed with tuberous sclerosis complex and intellectual disability found that one child with ASD exhibited an over 90% decrease in seizure frequency and an 80% decrease in injurious behaviors concurrently when undergoing VNS (46). Hu et al. demonstrated that VNS stimulation led to increased vagal activity, resulting in improved social skills and parent-child interactions and positive socioemotional outcomes for children with ASD (46). Wang et al. found that VNS improved linguistic and cognitive performance in children with ASD (19). Thus, VNS may serve as a potential adjunctive intervention for children with ASD.

There is only one branch of the vagus nerve on the surface of the body, the auricular branch (20). In neuropsychiatric disorders, taVNS stimulation of the auricular branch has gained significant attention. While the mechanisms of taVNS remain unclear, studies have discovered its effects in modulating socially relevant emotional and visceral states. ASD is a neurodevelopmental disorder involving structural abnormalities in several brain regions, including the supplementary motor area, somatosensory cortex, dorsal prefrontal cortex, premotor cortex, hippocampus, and basal ganglia (58). More importantly, evidence suggests that taVNS can activate brain regions associated with ASD, with electrical stimulation possibly propagating through a reverse pathway from peripheral nerves to the brainstem and central structures. This process may induce therapeutic effects by leveraging the “bottom-up” mechanisms of the central nervous system (21).

Functional nuclear magnetic resonance imaging studies of taVNS indicate enhanced blood oxygenation level-dependent signals in the amygdala, thalamus, and frontal cortex (59). It is consistent with brain activity modulation by implantable VNS. Furthermore, stimulation of the auricular tegmentum activates the amygdala and solitary fasciculus to a greater degree (59). These nuclei and brain regions may have close associations with brain regions experiencing functional deficits in individuals with HFA. In this study, patients will undergo clinical and imaging assessments during the baseline period. Additionally, clinical evaluations will be conducted during the short-term treatment period (W4), and clinical observations and neuroimaging investigations will be carried out immediately after treatment (W12), during the early follow-up period (W16), and throughout the late follow-up period (W24). This comprehensive approach enables a thorough examination of the therapeutic effects of taVNS on patients with HFA during the early stages of treatment, as well as the establishment of relatively stable brain network changes induced by taVNS. Furthermore, follow-up observations may shed light on the long-term stability of the taVNS-induced brain network alterations. Hopefully, with the most recent advances mentioned above, it is anticipated to uncover the effectiveness of taVNS and the underlying mechanisms with structural and functional magnetic resonance imaging in our study.

## Limitations

There are three limitations in this study. First, the sample size of this study may be sufficient to provide preliminary insights; however, it may not represent the entire population so generalizability may be limited. Second, the research was conducted at a single center. However, further observations utilizing taVNS in larger populations of children with HFA across multiple centers are certainly warranted. In addition, psychiatrists in our hospital have not received training in the use of Autism Diagnostic Observation Schedule-Second Edition (ADOS-2) and Autism Diagnostic Interview-Revised (ADI-R). Consequently, they are not certified to conduct evaluations using ADOS-2 and ADI-R.

## Conclusion

In light of the results of this study, it will be possible to optimize non-invasive neuromodulation therapies for children with HFA. Additionally, the results will shed light on how taVNS improves social skills in children with HFA. Our understanding of taVNS mechanisms and the pathogenesis of HFA will also be enhanced through the study of brain networks.

## Ethics statement

The studies involving humans were approved by ethics committee of Beijing Children’s Hospital. The studies were conducted in accordance with the local legislation and institutional requirements. Written informed consent for participation in this study was provided by the participants’ legal guardians/next of kin.
